### Auditing

The Postgraduate Program of the university will supervise the integrity of the data.

### Plans for communicating important protocol amendments to relevant parties

Any modification of the research procedures, including changes in the study objectives, study design, sample size, study procedures, or significant administrative aspects, will lead to a change in the study protocol. This will be under the supervision of the responsible professor ([name]) and approved by the Ethics Committee of the Federal University of São Carlos.

### Statistical analysis plan

Statistical analysis will be conducted with the aid of SPSS (version 22; SPSS Inc., Chicago, IL, USA). The normality and homoscedasticity of the data will be tested using the Shapiro–Wilk and Mauchly tests, respectively. If not normally distributed, data will be transformed to enable the use of parametric tests. All data will be expressed as mean and standard deviation.

Linear mixed models with two fixed factors will be applied to test associations between interventions (control, hip strap, and foot orthoses) and conditions (level-ground walking and single-leg squat test) as well as interactions between interventions and conditions. Linear mixed models were chosen due to the ability to include fixed and random effects and increase the study power by including individuals with missing data in the analysis. Subject and intercept will be included as random effects. The covariance type will be unstructured and the restricted maximum likelihood (REML) estimation method was chosen. When an interaction is significant, the mean difference (MD), standard error (SE), and *P*-value for the pairwise comparisons based on estimated marginal means will be reported. For all analyses, the significance level will be 0.05. Measures such as the 95% confidence interval (CI) and effect size will also be included. Interim analyses will not be performed. No additional analyses will be performed in the trial.

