#### Primary outcome

##### Pain intensity

Pain intensity will be measured using the visual analogue scale (VAS). This scale ranges from 0 to 100 mm, with the leftward extreme marked zero (absence of pain) and the rightward extreme marked 100 (worst pain imaginable). VAS scores will be computed by measuring the length of the line in millimetres from the extreme leftward mark (no pain) to the mark made by the participant. For the statistical purposes, the average score of the five valid attempts of each functional task will be used [33].

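### Mauchly's test is named as the homoscedasticity check, and a normality test on the data can move the primary VAS result off the mm scale

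*Protocol article*

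**What the plan says.** The section Statistical analysis plan of the protocol article fixes two checks: "The normality and homoscedasticity of the data will be tested using the Shapiro–Wilk and Mauchly tests, respectively". It fixes one action: "If not normally distributed, data will be transformed to enable the use of parametric tests". The next sentence reads: "All data will be expressed as mean and standard deviation".

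The model is then described: "Linear mixed models with two fixed factors will be applied to test associations between interventions (control, hip strap, and foot orthoses) and conditions", plus their interaction. On the covariance it says "Subject and intercept will be included as random effects" and "The covariance type will be unstructured and the restricted maximum likelihood (REML) estimation method was chosen". Mean differences between interventions, with standard errors and P-values, are promised when the interaction is significant; 95% confidence intervals are promised as well.

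The section Pain intensity defines the primary outcome as a 0 to 100 mm VAS and says that "the average score of the five valid attempts of each functional task will be used".

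The text does not mention residuals. It names no transformation and no back-transformation, attaches no action to Mauchly's result, and does not exempt the primary outcome.

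**The concern.** There are two faults in what is stated.

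- **The test does not match its purpose.** Mauchly's test asks whether the differences between repeated measures all have the same variance. It does not ask whether the measures, or the residuals, have equal variance.
- **The trigger does not match the model.** A linear mixed model assumes approximately normal residuals and random effects. Outcome values that mix two tasks with different pain levels, or that come from participants with very different pain, can look non-normal while the model fits well.

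At stake is the scale of the primary result. After a transformation the mean difference is no longer in mm and cannot be read directly on the VAS. The interaction is also tied to the scale, and under this plan it decides whether the pairwise comparisons are reported. The choice of scale would be made after seeing the data, by a test not directed at the model's assumptions.

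**Working it through.** **1. Inputs.**
- Sample size (section Sample): 26 plus 10%. 26 × 1.10 = 28.6, and 26 / 0.90 = 28.9; both round up to the stated 29. This figure is not disputed and is used below.
- Cells per participant: 3 interventions × 2 tasks = 6, so 29 × 6 = 174 values.
- Entry (section Sample) requires pain in at least two activities that load the patellofemoral joint, with squatting and stairs as examples. Pain on level walking is not required, so low or zero walking scores are plausible.
- The document gives no means, SDs or correlations for VAS. All such values below are assumptions.

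**2. What Mauchly's test detects** (three repeated measures, n = 29, 5,000 runs, level 0.05). Sphericity means that Var(Yi − Yj) = σii + σjj − 2σij is the same for every pair.
- Variances 300, 500, 900 with covariances 280, 480, 580: 300 + 500 − 560 = 240; 300 + 900 − 960 = 240; 500 + 900 − 1160 = 240. Sphericity holds while the variances differ threefold. Rejection: 5.2%.
- Equal variances of 400 with correlations 0.9, 0.3, 0.3: 2 × 400 × 0.1 = 80, and 2 × 400 × 0.7 = 560 twice. Variances are equal and sphericity fails. Rejection: 99.9%.
- Compound symmetry, for reference: 5.3%.

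The test missed a threefold difference in variance and rejected almost always when variances were equal. It is not a check of homoscedasticity.

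**3. Outcome values against residuals.** Data were generated exactly from a random-intercept model with task means (2,000 runs), so no transformation is needed. Share of trials with Shapiro–Wilk P < 0.05:

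| Assumed mean walk / squat (mm); SD between / within | All 174 values pooled | At least one of six cells | Residuals |
|---|---|---|---|
| 30 / 50; 15 / 10 | 7% | 24% | 5% |
| 20 / 60; 15 / 10 | 41% | 25% | 5% |
| 20 / 60; 10 / 8 | 98% | 26% | 5% |

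The pooled rate grows because two separated task means give a two-humped distribution. The any-cell rate is mainly multiplicity: six independent 5% tests would give 1 − 0.95^6 = 26.5%. The residuals stay at the nominal 5%.

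**4. The floor at 0.** One cell, latent normal with SD 15 mm, values below 0 set to 0, n = 29. The share at 0 is Φ(−mean/15).

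| Assumed latent mean (mm) | Share at 0 | Shapiro–Wilk rejection |
|---|---|---|
| 10 | 25% | 90% |
| 15 | 16% | 57% |
| 20 | 9% | 20% |
| 25 | 5% | 6% to 7% |
| 30 | 2% | 5% |

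Where rejection is frequent the values really are non-normal. But a cluster of tied zeros remains a cluster of ties under any monotone transformation, so transforming would not make them normal.

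**5. Scale and interaction.** Suppose an intervention lowers pain by 10 mm in both tasks: 30 to 20 and 60 to 50.
- In mm: −10 and −10, no interaction.
- Square root: 5.477 − 4.472 = 1.005, and 7.746 − 7.071 = 0.675, an interaction.
- Log: ratios 20/30 = 0.67 and 50/60 = 0.83, an interaction.

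The reverse also occurs. A 30% fall in both tasks, 15 to 10.5 and 40 to 28, is −4.5 against −12 mm, but a ratio of 0.70 in each. The log and square root are illustrations only, since the plan names neither.

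**The case against.** The other side has real points.

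- **A reader might infer that the plan tests raw outcome values.** It says only that the data are tested. Nothing points to residuals, but a fuller plan could apply the test to them, and the trigger rate would then be about 5% when the model is right. This stands as a limit on the size of the problem. The sentence still needs to say which is meant.
- **A reader might infer that Mauchly's test has no bearing on this model.** That goes too far. A random intercept with independent residuals implies compound symmetry, and hence sphericity, so the test touches a property of the model. The fault is the purpose assigned to it. The practical harm is small because no action depends on the result.
- **The unstructured covariance may already allow unequal variances.** If the term refers to the repeated measures, variance by task is already free. If it refers to a lone random intercept, it adds nothing. The text does not settle this.
- **A reader might infer a log transformation that fails at zero.** None is named, and others accept zeros. What survives is that any non-linear transformation leaves the mm scale and can change the interaction.
- **A reader might infer that the primary result could go unreported because of this rule.** The restriction of pairwise comparisons to a significant interaction is a separate rule. The plan also promises means and SDs, confidence intervals and effect sizes, so descriptive results in mm could still appear.
- **The simulated rates are conditional.** The figure of about 25% assumes six separate tests, which the plan does not state. The high rates under flooring need a latent walking mean of 15 mm or less. No simulation here shows bias or a changed type I error in the primary estimate.

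**Conclusion.** The point holds in a limited form. As written, the plan assigns homoscedasticity to a test of sphericity, so the stated check is not carried out. It also orders a transformation when the data fail a normality test, with the primary VAS outcome included. Both are stated rules, not details left out of a condensed article.

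Followed as written, the second rule can take the primary mean difference off the mm scale when the mixed model is adequate, and can alter the interaction that gates the pairwise comparisons. The frequency cannot be fixed from the document. At n = 29 it is about 25% if six normal cells are tested one by one. It is 7% to 98% if all values are pooled, depending on the assumed task means and SDs, and about 5% if residuals are tested. For a single cell floored at 0 with SD 15 mm, it rises from about 5% at an assumed latent mean of 30 mm to 90% at 10 mm.

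This does not invalidate the trial, and the harm is conditional. It should be corrected before data collection, because afterwards the choice of scale would be open to influence from the results.

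**What to change.** In the section Statistical analysis plan:

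1. Delete Mauchly's test as the check of homoscedasticity.
2. Delete the transformation rule for the primary outcome, and state that VAS pain is analysed and reported in mm in all cases.
3. State that assumptions are checked on the residuals of the fitted model, plotted by task and intervention.
4. Allow the residual variance to differ by task, and say whether the unstructured covariance refers to the random effect or to the repeated measures.
5. Name one fallback: if residuals are clearly non-normal, keep the mean differences in mm and take 95% confidence intervals from a bootstrap that resamples whole participants. Other robust methods, such as a within-participant permutation test, would also serve; what matters is that one is named in advance. It has to be written into the plan, because the section rules out further analyses.

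The cost is a few lines of analysis wording and a short script. No data or participants are affected, and the section Trial status says that recruitment has not begun.

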**Methods:**

Twenty-nine individuals with PFOA aged 50 years or older will take part in the study. The main outcome is pain intensity. The secondary outcomes are other self-reported measures (global rating of change, acceptable state of symptoms, ease of performance, and confidence) and lower limb kinematics (peak femoral adduction and internal rotation, and peak rearfoot eversion). These outcomes will be assessed during functional tasks performed under three conditions: (i) control condition, (ii) hip strap intervention, and (iii) foot orthoses intervention. To investigate whether these interventions result in the lower limb kinematic changes that they are purported to cause, three-dimensional kinematics of the femur and rearfoot will be captured during each task. Linear mixed models with two fixed factors will be used to test associations between the interventions (control, hip strap, and foot orthoses) and conditions (level-ground walking and single-leg squat test) as well as interactions between the interventions and conditions.

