#### Secondary outcomes

##### Global rating of change (GRC) scale

The patient’s perception of improvement or deterioration will be quantified using a GRC scale, which is a 15-point Likert-type scale that measures the patient’s impression of a change in health status following a specific treatment [40]. The scale ranges from − 7 (great deal worse) to + 7 (great deal better), with 0 indicating no change. Changes of 4 points or more on this scale have been previously considered clinically important in patients with knee pain [41, 42]. This scale will be applied for both conditions (hip strap and foot orthoses).

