##### Acceptable state of symptoms

The acceptable state of symptoms will be assessed by asking the participants the following question: “Considering your usual level of pain and your functional disability to perform daily tasks, if you performed this functional task (level-ground walking or single-leg squat test) with the approach used in this intervention (hip strap or foot orthoses) from now on, would you consider your current state to be satisfactory?” [43]. The participants will answer “yes” or “no”. The question will be posed for both conditions (hip strap and foot orthoses).

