##### Ease of performance

To assess the ease of performance during each task, the participants will use a 5-point Likert scale to rate how easy each test was to perform: (i) markedly hard, (ii) somewhat hard, (iii) neither hard nor easy, (iv) somewhat easy, or (v) markedly easy [22].

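### The single stated analysis, a three-level linear mixed model with mean and SD, does not fit global rating of change or acceptable state of symptoms: neither has control data, and the second is a yes/no item.

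*Protocol article*

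**What the plan says.** The protocol's Statistical analysis plan section gives one inferential method and limits it to no particular outcome: "Linear mixed models with two fixed factors will be applied to test associations between interventions (control, hip strap, and foot orthoses) and conditions", the second factor being the two tasks, with their interaction. Three general rules accompany it:

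- Summaries: "All data will be expressed as mean and standard deviation".
- Non-normality: "If not normally distributed, data will be transformed to enable the use of parametric tests".
- Scope: "No additional analyses will be performed in the trial".

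The outcome sections describe data of a different kind. Under Global rating of change (GRC) scale, a score from −7 to +7 with 0 as no change: "This scale will be applied for both conditions (hip strap and foot orthoses". Under Acceptable state of symptoms, a question answered yes or no: "The question will be posed for both conditions (hip strap and foot orthoses". Control is named in neither place.

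The abstract's Methods paragraph lists both among the secondary outcomes and then says "These outcomes will be assessed during functional tasks performed under three conditions", control being the first of the three.

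**The concern.** A model with a control level needs control data. For GRC and acceptable state the protocol collects none, so the stated model asks for contrasts that the data cannot supply. Acceptable state has a second problem: the mean-and-SD summary and the transform-to-normality rule were written for continuous measurements.

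These are positive rules that do not fit listed outcomes, not details left to a fuller plan. If they stand, the analyst must either follow them where they do not work or choose another method after the data are in, which the scope sentence appears to forbid. The primary aim is stated in terms of self-reported outcomes, and the hypothesis covers the other self-reported measures as well as pain, so these two results will be read as part of the main message.

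**Working it through.** **Inputs.** Intervention levels: 3. Tasks: 2 (Statistical analysis plan). Levels with data for GRC and acceptable state: 2 (their own sections). Planned sample: 29, or 26 before the dropout allowance (Sample). The documents give no expected proportion answering yes, so those used below are assumptions.

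**1. Empty cells.** The full layout has 3 × 2 = 6 cells, the same six that the Sample section counts. Without control, 2 × 2 = 4 remain, so 2 of 6 are empty by design for every participant.

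The fixed part of the stated model has 1 intercept + 2 intervention terms + 1 task term + 2 interaction terms = 6 parameters. With all six cells filled the design matrix has rank 6. With control removed it has rank 4. Two consequences follow:

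- Neither device-versus-control contrast is estimable.
- The interaction falls from (3−1)(2−1) = 2 degrees of freedom to (2−1)(2−1) = 1.

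The mixed model's tolerance of missing data does not help, because nobody contributes a control value.

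**2. Transformation of a yes/no item.** Let y be 0 or 1 and f any transformation. Then f(y) = f(0) + [f(1) − f(0)]·y, which is only a linear rescaling. The transformed variable still has two values, and the model gives the same test statistics. In simulated samples of 29 with 50%, 70% or 90% yes (2,000 runs each), Shapiro–Wilk rejected normality in 100%. Samples with identical answers throughout, where the test is undefined, were counted as rejections. The plan's trigger would therefore fire, and its remedy could not work.

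**3. Summary by mean and SD.** The SD of a yes/no item is √[p(1−p)]: 0.50 at p = 0.5 and 0.30 at p = 0.9. It adds nothing to the proportion. A normal 95% interval at p = 0.9 and n = 29 is 0.9 ± 1.96·√(0.09/29) = 0.9 ± 0.109, or 0.79 to 1.01, which passes the maximum possible value of 1.

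**4. Error rates within task.** Assume 90% yes in one task and 50% in the other, with no true difference between devices. The variances are 0.09 and 0.25. A model with one residual variance uses about (0.09 + 0.25)/2 = 0.17 in both tasks. Treating answers as independent, a nominal 5% test within a task has these approximate error rates:

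| Task | Effective critical value | True error |
|---|---|---|
| 90% yes | 1.96·√(0.17/0.09) = 2.69 | 0.7% |
| 50% yes | 1.96·√(0.17/0.25) = 1.62 | 10.6% |

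A simulation of a random-intercept linear model on yes/no data gave 0.7% and 8.2% for the same contrasts. The overall device and interaction tests held up better: 3.8 to 3.9% in this setting, and 4.5 to 5.0% when the proportions were 50/50 or 70/50.

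**5. The two descriptions of collection.** The abstract says all listed outcomes are assessed under three conditions. The GRC and acceptable-state sections say two. Both cannot be right; the outcome sections are the more specific.

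**The case against.** Several stronger readings are tempting, and the documents do not support them.

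- *These analyses cannot be run at all.* With no control rows, the same model reduces to strap versus orthoses by task, which is estimable. What is lost is the control contrast; what is missing is a statement that two levels are meant.
- *GRC has no comparator.* It measures change after a specific treatment, and 0 means no change. Omitting control is a defensible design choice, and a device mean with its 95% CI already speaks to improvement.
- *The 5-point ease-of-performance rating is also wrongly analysed.* The protocol says "the participants will use a 5-point Likert scale to rate how easy each test was to perform", and a linear model on such a rating is a common approximation. A null simulation with 26 participants and assumed distributions gave 4.9 to 5.1% for the device and interaction tests when the tasks were similar, and 4.0 to 4.5% when they were very different. Within-task contrasts in the latter case were 2.7% and 6.4%. That is a matter of degree.
- *The mean of a yes/no item is meaningless.* It is the proportion answering yes. The SD and the normality rule are what do not fit.

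Three further points can be made in defence. The exclusion of additional analyses follows directly after the sentence on interim analyses, so it may be aimed at extra analyses, not at a suitable method for a listed outcome. The section never says outcome by outcome what the model covers. It also specifies an unstructured covariance; if that governs the repeated measures and not just the random intercept, variances may differ between cells and the distortion in step 4 would shrink. These points soften the reading. They do not supply control data, and they do not reconcile a rule for all data with a yes/no item.

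**Conclusion.** The point holds for two of the four secondary self-reported outcomes. For GRC and acceptable state, 2 of 6 cells are empty and the device-versus-control contrasts are inestimable; this is arithmetic and needs no assumption. For acceptable state, it is equally certain that transformation cannot produce normality.

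The size of the error-rate problem is conditional. It concerns within-task comparisons, depends on the proportion differing markedly between tasks, and rests on chosen proportions and a single residual variance. At 90% and 50% it is material (0.7% and 8.2% against a nominal 5%); the overall tests are little affected.

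A reader might infer that the trial's main result or most of its secondary analyses are compromised. They are not: pain intensity, knee confidence and kinematics fit the stated model as far as this point goes. The sentence in the abstract is a wording slip, but it describes control data that will not be collected. The changes should be made, and they do not affect the design or the sample size.

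**What to change.** In the Statistical analysis plan section:

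1. **GRC.** State that it is analysed as hip strap versus foot orthoses by task, with each device's mean and 95% CI against 0 and the proportion at or above +4, the threshold that the protocol itself cites as clinically important.
2. **Acceptable state.** Report counts and percentages. Compare the two devices with a mixed logistic model or GEE, or with an exact McNemar test within each task. Exempt this outcome from the mean-and-SD and transformation rules.
3. **Abstract.** Correct the Methods sentence to say that GRC and acceptable state are assessed under the two device conditions only.

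Two further steps are optional. An ordinal model for ease of performance could be added as a sensitivity analysis; it is not a correction. The acceptable-state question could also be asked under control, but it refers to the device in use and would have to be reworded, so this means changing the instrument.

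The required changes are text only, with no new data and no change to the 29 participants. The Trial status section says recruitment has not started, and the protocol provides a route for amendments through the ethics committee.

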### Study design and setting

A within-subject randomised crossover study will be conducted. This is the original version of the study protocol, which has been submitted to the *Clinical Trials* registry (clinicaltrials.gov) and was registered on 3 April 2020 under identification code NCT04332900.

The research will be conducted at the Evaluation and Intervention in Orthopaedics Laboratory (LAIOT) of the Physical Therapy Department of the Federal University of São Carlos (UFSCar) at a controlled temperature (21 to 23 °C).

The following methodology strictly follows the Standard Protocol Items: Recommendations for Interventional Trials 2013 checklist (SPIRIT) [26] and Template for Intervention Description and Replication (TIDieR) [27] to improve the information and quality of intervention reporting [28]. Additional File 1 presents the SPIRIT checklist. Consolidated Standards of Reporting Trials (CONSORT) [29] will be followed for reporting the results in a subsequent article.

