### Randomisation and masking

The participants will perform the tasks under three conditions (control condition, hip strap intervention, and foot orthoses intervention) in random order, which will be defined by a random number generator programme (www.randomization.com). Allocation concealment will be achieved using sequentially numbered opaque sealed envelopes. The order will be disclosed until the participants sign the statement of informed consent. A researcher not involved in the assessment or data collection processes will perform the randomisation step. This researcher also will be responsible for obtaining signed informed consent from the participants.

Due to the nature of the interventions administered in this study, the participants, the assessor who will administer the interventions, and the assessor who will conduct the data collection will not be blinded. Blinding will only be performed during the data processing and statistical analysis steps. The researcher conducting these steps will be blinded to the condition to which each participant was assigned. Thus, unblinding will not occur.

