### Procedures

The participants will undergo a single session. At the beginning of the session, information will be collected on age, duration of symptoms, level of kinesiophoebia determined using the Tampa Scale of Kinesiophobia [32], usual and worst levels of pain experienced in the previous week using the visual analogue scale (VAS) [33], and symptoms related to the knee using the Anterior Knee Pain Scale (AKPS) [34] and Knee Injury and Osteoarthritis Outcome Score (KOOS-BR) [35]. Anthropometric and demographic data will also be collected for the characterisation of the study population. The MMSE [36] will be used to assess cognitive function and the ability to participate in the study. Cut-off points will be determined taking into account the educational level of each participant [36].

The participants will be assessed during level walking at a self-selected pace and the single-leg squat test under the three conditions, the order of which will be randomised: (i) control condition, (ii) hip strap intervention, and (iii) foot orthoses intervention. The control refers to the condition in which no interventions will be administered. The design of the study is shown in Fig. 1.

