**Fig. 1 Fig1:**
[figure not shown]
Study design

The assessment will be performed on the affected lower limb in cases of unilateral PFOA or on the more painful knee in cases of bilateral PFOA [24]. If the participant reports equal pain intensity in both lower limbs, the lower limb to be tested will be chosen randomly using a simple raffle. For all evaluations, the participants will wear shorts, sports tops (in the case of women), and the same type of shoes (Nike® model *Flex Experience RN 2 MSL*), which will be provided to them by the assessors. The primary and secondary outcomes will be investigated during the performance of two functional tasks: level-ground walking and single-leg squat test.

Data collection and the therapeutic implementation steps will be performed by different assessors during the entire course of the study. Prior to data collection, the participants will have a period of familiarisation with both functional tasks and both therapeutic approaches that will be applied. The participants will perform the two functional tasks in a standardised order. The first will be level-ground walking at a self-selected pace and second will be the single-leg squat test, which is associated with a progressively larger patellofemoral joint load.

The presence of any pain or disability that may be related to the interventions and/or functional tasks will be considered as the criterion to discontinue the study.

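### The planned mixed models leave out period in a single-session crossover on provoked pain, so any drift over the session goes into the error; the text also does not say whether the six orders are balanced

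*Protocol article*

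**What the plan says.** Under Study design and setting: "A within-subject randomised crossover study will be conducted". Under Procedures: "The participants will undergo a single session". The three conditions are control, hip strap and foot orthoses, so there are six possible orders. Randomisation and masking says that they are performed "in random order, which will be defined by a random number generator programme", with sealed envelopes; it neither states nor rules out blocking or equal numbers per order.

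Within the session, "The participants will perform the two functional tasks in a standardised order": walking first, then the single-leg squat. Each task needs five valid trials, with one minute between trials. No interval between conditions is given in the text.

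The Statistical analysis plan section fixes the model: "Linear mixed models with two fixed factors will be applied to test associations between interventions" and tasks, plus their interaction. It adds "Subject and intercept will be included as random effects" and "The covariance type will be unstructured and the restricted maximum likelihood (REML) estimation method was chosen". Neither period nor sequence appears. The section ends with "No additional analyses will be performed in the trial".

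**The concern.** In a three-period crossover, period is a known source of variation and is normally in the model. Here a period effect is plausible from the design alone. Eligibility requires anterior knee pain brought on by patellofemoral loading. Each person then completes at least 15 valid single-leg squats (5 in each of 3 conditions), and invalid attempts are repeated. On the natural reading, walking in the first period precedes all recorded squats, while in the second and third periods it follows 5 and 10 of them. A period effect could therefore differ between the tasks.

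The omission cannot be put down to detail held elsewhere. The section names its fixed factors and closes the list, so as written a period adjustment is shut out. At stake are the width of the intervals for the primary outcome and, on one reading of the covariance statement, the type I error for the intervention effect.

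**Working it through.** **Inputs from the protocol.** Three conditions, two tasks, one session, random order, and 29 participants (26 plus 10%: 26 × 1.10 = 28.6, rounded up). The plan gives no figure for a period effect or for a residual SD in millimetres, so there is none to reproduce on this point.

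**Assumptions.** Drift is linear at δ mm per period on the 100 mm scale, the within-person residual SD is σ, and data are complete. Several pairs of values are shown because the document supports none in particular.

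**One task, no period term.** Over the six orders, the gap in period between a device and control is ±1 in four orders and ±2 in two. Its mean is 0 and its mean square is (4×1 + 2×4)/6 = 2. The mean of 0 is why the estimate is unbiased over the randomisation. The variance of one person's device-minus-control difference rises from 2σ² to 2σ² + 2δ², so

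SE = √[(2σ² + 2δ²)/29], and the ratio to the no-drift SE is √(1 + δ²/σ²).

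| δ (mm) | σ (mm) | SE, no drift | SE, drift ignored | Rise by formula | Rise against a fitted period model (simulated) |
|---|---|---|---|---|---|
| 3 | 10 | 2.63 | 2.74 | 4% | about 2% |
| 5 | 15 | 3.94 | 4.15 | 5% | about 3% |
| 5 | 8 | 2.10 | 2.48 | 18% | about 16% |
| 10 | 15 | 3.94 | 4.73 | 20% | about 18% |
| 8 | 8 | 2.10 | 2.97 | 41% | about 39% |

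The last column is lower because fitting period itself costs about 2% in SE under unrestricted orders (3.98 against 3.90 mm with no drift and σ = 15).

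**Power.** In simulation with σ = 15 and a true effect of 10 mm, power with period fitted is 68–69% at every drift. Without it, power is 70%, 68%, 67% and 54% at drifts of 0, 2.5, 5 and 10 mm.

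**Shift given the orders drawn.** If orders are drawn without restriction, the device-minus-control difference in mean period has SD √(2/29) = 0.263. The estimate then moves by chance with SD 0.263δ: 1.3 mm at δ = 5, 2.1 mm at δ = 8 and 2.6 mm at δ = 10. This is the same quantity as the SE rise: at δ = 5 and σ = 8, √(178/29 − 128/29) = √(50/29) = 1.3 mm. Permuted blocks of six cut the SD of the gap to 0.049, with a maximum of 2/29 = 0.069.

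**Both tasks in one model, unrestricted orders.** A period shift is common to both tasks within a condition. If the only random term is a subject intercept, the model treats the two tasks as independent given the person, and the error is understated. Simulated type I error for the intervention effect is about 6% (δ/σ = 3/10 and 5/15), 9–12% (5/8), about 11% (10/15) and 12–16% (8/8). The ranges reflect separate simulations and whether one contrast or the overall test is used. With period fitted it is about 5%. A paired contrast, which is what an unstructured covariance over the six cells gives with complete data, stays near 5% without period.

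**Blocking alone.** With blocks of six and no period term, the drift stays in the residual. At δ = 10 and σ = 15, one-task type I error falls to 2.2%, and power is 53% against 69% with period fitted. The chance shift is nearly gone, but the intervals are too wide.

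**The case against.** The strongest reply is that random order already protects the comparison. That stands. A reader might infer that omitting period biases the device effects. It does not do so systematically: simulated means were −0.11 to 0.04 mm for a true 0 and 9.86 to 10.06 mm for a true 10 under unrestricted orders. Only a chance shift remains, and for a single task under unrestricted draws the wider SE already covers it (type I error 4.6–5.2%). It should not be counted as a second harm.

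A reader might also infer that the orders are unbalanced. The protocol is silent on this, and an article commonly leaves block details to the full protocol.

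Nor does any section say that pain rises over the session. Familiarisation and the one-minute rests may limit a drift. That the conditions follow without a break, and that both tasks are finished in one condition before the next begins, are inferences; the design figures are not shown. At the smaller drifts the net loss is 2–3%.

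Finally, the type I error concern depends on how the covariance statement is read, and the text does not settle whether the unstructured form applies to the random effect or to the six repeated cells.

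None of this answers the omission itself, which is fixed in the text and closed to later additions.

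**Conclusion.** The point holds as a precision problem that is cheap to correct. The model omits a known design factor, and the plan leaves no room to add it. The SE rise ranges from about 4% to 41% before the roughly 2% cost of fitting period, depending on assumed drifts of 3 to 10 mm per period and residual SDs of 8 to 15 mm. With little or no drift nothing material is lost. An inflated type I error, about 6% to 16% over the same assumptions, follows only if both tasks share a bare random intercept and orders are unrestricted. The documents support neither a claim of systematic bias nor a claim that the orders are in fact unbalanced.

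**What to change.** Add period (1 to 3) and period-by-task as fixed effects to the mixed models for outcomes measured under all three conditions: pain, ease of performance, knee confidence and kinematics. Global rating of change and acceptable state are asked only for the two devices; for these, compare the devices in a way that takes account of their period.

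State in Randomisation and masking that the six orders are allocated in permuted blocks of six (five blocks, 30 envelopes), if this is not already done. Blocking complements the period term and does not replace it.

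The cost is up to 4 degrees of freedom (2 for period, 2 for period-by-task) and about 2% in SE if there is no drift. Trial status says that recruitment has not started, so both changes can be made before any data are collected.
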